**Hypothesis** **3a1.**
*Basic psychological need satisfaction and autonomous motivation will mediate the relationship between the coach’s controlling interpersonal style and healthy lifestyle in both the face-to-face and semi face-to-face modalities, at baseline and post-intervention.*

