**Hypothesis** **4.**
*The type of participation (face-to-face and semi face-to-face) will moderate the relationships between the following both at baseline and after the intervention: (a) the coach’s controlling interpersonal style and basic psychological need satisfaction; (b) basic psychological need satisfaction and autonomous motivation; (c) autonomous motivation and healthy lifestyle; and (d) autonomous motivation and burnout.*

Specific Objective 5. To analyze the acceptability of the PsicoFIT intervention and the perceived contribution by participants in terms of motivation toward physical activity, psychological well-being, and psychological ill-being in both the face-to-face and semi face-to-face modalities.

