#### 2.3.3. Assessment Timeline

Evaluations will be conducted at the following times:Time 1. Week 0: What is My Lifestyle Like? Survey.Time 1. Week 2: Controlling Coach Behaviors Scale, Perceived Autonomy in Sport Scale, Perceived Competence Scale, Need for Relatedness Scale, Sport Motivation Scale II, and Athlete Burnout Questionnaire. The questionnaires will be administered at this point because they will assess the variables that require the participants to have previously interacted with the program components in order to be appropriately perceived.Time 2. Week 13: All instruments and the focus group will be administered.

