Intervention-related changes. Changes in the coach’s controlling interpersonal style, basic psychological need satisfaction, autonomous motivation, healthy lifestyle, and burnout from baseline to post-intervention will be examined. Within-group pre-post comparisons will be conducted for each intervention modality (face-to-face and semi-face-to-face). Between-group comparisons will assess whether the magnitude of changes differs between the two modalities [42]. Effect sizes will be calculated to quantify the magnitude of the observed changes, and statistical power will be considered in interpreting the results [113].

Mediation effects. The effects of basic psychological needs satisfaction and autonomous motivation as mediating variables (the mediation effect of basic psychological needs satisfaction and autonomous motivation on the relationship between the coach’s controlling interpersonal style, healthy lifestyle, and burnout, as well as the effect of basic psychological needs satisfaction on the relationship between autonomous motivation, healthy lifestyle, and burnout) will be evaluated using regression-based mediation analyses with bootstrapping procedures to estimate direct and indirect effects following Hayes’s recommendations [43], considering pre- and post-intervention data. The significance of mediation inferred when the confidence interval of the indirect effect does not include zero allows for the assessment of whether the observed relationships are explained directly or indirectly through the proposed mediating variables. Mediation effects will be considered exploratory due to the sample size and the nature of the study.

Moderation Effects. The moderating effects of both intervention modalities will be evaluated using regression-based moderation analyses, following Hayes’s recommendations [43], considering both pre- and post-intervention data. Moderation will be examined by including interaction effects, as evaluated through bootstrapped confidence intervals. Significant interaction effects will indicate that the strength or direction of the relationship between predictors and outcomes differs according to the intervention modality. Moderation effects will be considered exploratory due to the sample size and the nature of the study.

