#### 2.7.2. Secondary Outcomes

Basic psychological needs satisfaction: Changes in autonomy, competence, and relatedness will be evaluated as potential mediators of the intervention’s effects.Autonomous motivation: Autonomous motivation, composed of intrinsic, identified, and integrated regulation, will be evaluated as a mechanism mediating the effects of the intervention on healthy lifestyle and burnout.Controlling interpersonal coaching style: The perception of control and pressure exerted by the coach, including task imposition and reward manipulation, will be assessed as a contextual predictor to understand its influence on the intervention effect sequence.

The metric for all secondary outcomes will be the change in total post-intervention scores relative to baseline.

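### Baseline mediation and moderation models with lifestyle as outcome use an outcome recorded before its predictors, and no planned mediation model tests the stated claim that needs and motivation mediate the intervention's effects

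*Protocol article*

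**What the plan says.** **Timing.** Section 2.3.3 splits time 1 into two occasions. Lifestyle comes first: "Time 1. Week 0: What is My Lifestyle Like? Survey". The remaining scales follow: "Time 1. Week 2: Controlling Coach Behaviors Scale, Perceived Autonomy in Sport Scale", together with the competence, relatedness, motivation and burnout questionnaires. The reason given is that these variables "require the participants to have previously interacted with the program components". Table 1 agrees and shows both modalities being delivered from week 1.

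**Hypotheses at baseline.** Hypothesis 3a1 states that needs and motivation "will mediate the relationship between the coach’s controlling interpersonal style and healthy lifestyle", at baseline and post-intervention. Hypothesis 3b1 does the same for motivation between needs and lifestyle. Hypothesis 4 adds: "The type of participation (face-to-face and semi face-to-face) will moderate the relationships between the following both at baseline and after the intervention". Its item (c) is the relation of motivation to lifestyle.

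**Purpose of the mediators.** Section 2.7.2 says of autonomous motivation that it "will be evaluated as a mechanism mediating the effects of the intervention on healthy lifestyle and burnout", and gives needs satisfaction a similar role as a potential mediator. The Abstract speaks in the same terms.

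**Models.** Section 2.6.1 specifies regression-based mediation with bootstrapping, "considering pre- and post-intervention data". It infers mediation when the interval for the indirect effect excludes zero, and labels mediation and moderation exploratory. Modality is a stratum in the mediation hypotheses and the moderator in Hypothesis 4. Section 2.1 states that there is no untreated control group.

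**The concern.** A mediation model assigns a direction: exposure acts on mediator, mediator acts on outcome. If the outcome was recorded two weeks before the exposure and the mediator, the model cannot speak to that direction, however the interval falls. The protocol's own reason for the week-2 timing sharpens this, because it says these variables need prior contact with the programme in order to be perceived. When week-0 lifestyle was recorded, there was no programme coach to perceive. An interval that excludes zero would still be read as mediation under the stated rule.

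The second problem is a mismatch between purpose and model. To say that a variable mediates the intervention's effects, some contrast in the intervention must be the exposure. With no untreated arm, modality is the only randomised contrast, and it is not the exposure in any mediation model. A report following this plan could present an indirect effect of perceived coach style as evidence on how the intervention works, which it is not.

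**Working it through.** The plan gives no path values, effect sizes or power for these models, so there is no figure to reproduce. The check is a cross-tabulation of models against measurement weeks, followed by two illustrations.

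**1. Measurement weeks at time 1** (section 2.3.3, Table 1)

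- Lifestyle: week 0
- Coach style, needs, motivation, burnout: week 2
- Delivery starts: week 1

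**2. Mediation fits** (Objectives 3a and 3b)

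| Effect | Exposure → mediator(s) → outcome | Outcome week | Predictor week | Reversed at time 1 |
|---|---|---|---|---|
| 1 (H3a1) | coach style → needs, motivation → lifestyle | 0 | 2 | yes |
| 2 (H3a2) | coach style → needs, motivation → burnout | 2 | 2 | no |
| 3 (H3b1) | needs → motivation → lifestyle | 0 | 2 | yes |
| 4 (H3b2) | needs → motivation → burnout | 2 | 2 | no |

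Taking one fit per modality and occasion, as the hypotheses are worded: 4 effects × 2 modalities × 2 occasions = 16 fits. Reversed: 2 effects × 2 modalities × 1 occasion = 4. Fits with modality as exposure: 0 of 16.

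**3. Moderation fits** (Objective 4)

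4 effects × 2 occasions = 8 fits. Reversed: effect 3 (motivation and lifestyle) at time 1, so 1 of 8.

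At week 13 all scales are taken together, so those models are cross-sectional but not reversed.

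**4. Illustration: how often a model with the arrow the wrong way declares mediation.** The paths are assumptions; the documents give none. Let lifestyle L and perceived coach style C be independent with unit variance, and let motivation be M = pL − pC + e, with M scaled to unit variance. Nothing acts on L. Fit C → M → L:

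- C to M: −p
- M to L given C: p / (1 − p²)
- apparent indirect effect: −p² / (1 − p²); the true effect is 0

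| p | Apparent indirect effect | 95% bootstrap interval excludes 0, n = 40 |
|---|---|---|
| 0.4 | −0.16/0.84 = −0.19 | about 60% |
| 0.3 | −0.09/0.91 = −0.10 | about 24% |
| 0.2 | −0.04/0.96 = −0.04 | about 5% |
| 0.1 | −0.01/0.99 = −0.01 | about 1% |

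The percentages are simulated and vary by a point or two between runs. n = 40 is one full modality. The model has one mediator, whereas Hypothesis 3a1 has two.

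**5. Illustration: whether the planned models inform on mediation by modality.** Simulated with 40 per modality and 4,000 runs, again with assumed paths.

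| Scenario | True modality indirect effect | Planned within-modality indirect effect | Modality-as-exposure model |
|---|---|---|---|
| Modality has no effect on M; X→M = 0.5, M→Y = 0.5 | 0 | 0.25 | 0.00 |
| Modality→M = 0.8, M→Y = 0.5; X→M = 0 | 0.8 × 0.5 = 0.40 | 0.00 | 0.40 |

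X is the psychological exposure. The planned indirect effect can be sizeable when modality mediates nothing, and zero when modality acts through the mediator.

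**6. A related inconsistency.** Objective 3b and Hypotheses 3b1 and 3b2 place motivation between needs and the outcomes. The mediation paragraph of section 2.6.1 instead describes needs as acting on the relation between motivation and the outcomes. The two cannot both describe the same model. Modality is not the exposure under either reading.

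**The case against.** **The models are labelled exploratory, and the primary outcomes do not depend on them.** True, and it limits the weight of the point. The label rests on sample size and the nature of the study. It neither restores time order nor supplies a missing exposure.

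**Modality is not ignored.** Section 2.6.1 compares changes in needs and motivation between modalities, which bears on the path from modality to mediator, and Hypothesis 4 tests modality as moderator of each link. This stands. What is absent is a model that joins the paths into an indirect effect.

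**The false-positive illustration depends on the chosen paths and is not about timing.** Both parts stand. The rate falls from about 60% to about 1% across the range shown, and the same figures would arise if everything had been measured in one week. It shows reverse causation in mediation models generally. The timing makes the plan's intended direction untenable for the reversed fits, but the simulation does not measure the cost of the two-week gap.

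**Stronger readings that the documents do not support.** A reader might infer that all time-1 analyses are invalid. Hypothesis 1 and its regressions claim only association, which needs no time order, and the burnout models take outcome and predictors in the same week. A reader might also infer that modality could not possibly moderate the time-1 relation of motivation to lifestyle. Motivation is measured in week 2, after delivery began, so modality could alter that association. It could not alter an effect of motivation on lifestyle already recorded.

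**Adding modality would not isolate PsicoFIT.** Correct. Sections 2.4.2 and 2.4.3 show that training and nutrition also differ by modality, and there is no untreated arm. Such a model addresses only the between-modality difference of the whole programme.

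**Conclusion.** The point holds within a limited scope. Four of 16 mediation fits and one of 8 moderation fits, all at time 1 with lifestyle as outcome, cannot support the directional hypotheses assigned to them. This follows from the stated measurement weeks and needs no assumption beyond counting one fit per modality and occasion. Separately, the description of needs and motivation as mediators of the intervention's effects matches none of the 16 mediation fits and would remain untested.

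The simulated rates are illustrations under assumed paths and should not be quoted as the error rate of this trial. The primary change-score comparisons are untouched. The point should be corrected before analysis, but it does not threaten the trial's main results.

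**What to change.** 1. Drop the time-1 mediation and moderation tests with lifestyle as outcome (H3a1, H3b1 and item (c) of Hypothesis 4), or report them as non-directional associations. Replace them with models of week-13 lifestyle on week-2 coach style, needs and motivation, adjusted for week-0 lifestyle.
2. Reword the Abstract and section 2.7.2 so that needs and motivation are described through associations within modality. If a mechanism claim is kept, add an exploratory pooled model from modality to mediator to week-13 outcome, with a bootstrap interval, adjusted for sex and for the outcome's own earlier score (week-0 lifestyle; week-2 burnout). State the mediator's time point: week 2 is early in twelve modules, and week 13 coincides with the outcome. State also that the model addresses only the between-modality difference of the whole programme.
3. Reconcile the mediation paragraph of section 2.6.1 with Objective 3b on whether needs or motivation is the mediator.

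Cost: wording changes and a few re-specified models on data already planned. The downside is that the baseline lifestyle hypotheses are dropped or reworded.

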#### 2.6.2. Qualitative Analysis

Acceptability and Perceived Contribution. Participant responses and comments will be analyzed using the constant comparison method [44]. Units of analysis, corresponding to the participants’ opinions, will be systematically compared to identify patterns, differences, and nuances. These units will be categorized using the thematic affinity criterion.

Subsequently, conclusions from the focus group will be compared with the intervention objectives to determine acceptability and perceived contribution, as well as to propose improvements for future implementations.

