**Hypothesis** **5.**
*The psychoeducational intervention will achieve adequate acceptability, and participants will perceive a positive contribution in terms of motivation toward physical activity, psychological well-being, and psychological ill-being in both modalities.*

The development of this protocol will contribute to establishing methodological guidelines that, once examined, may guide future psychoeducational interventions in sports contexts, particularly those targeting sedentary and overweight adults, by providing a framework for the promotion of healthy habits and psychological well-being.

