## 2. Materials and Methods

### 2.1. Design

A mixed-methods convergent parallel approach will be adopted [40] within the framework of a longitudinal comparative pragmatic clinical trial [41]. To examine changes and to compare delivery modalities, the participants will be randomly assigned to receive the intervention in either a face-to-face or semi face-to-face modality, with measurements at time 1 (baseline) and time 2 (post-intervention).

Quantitative analyses will include hierarchical multiple regression analyses, pre-post comparisons, and regression-based mediation and moderation analyses [42,43]. Additionally, the acceptability and perceived contribution of the intervention will be explored using a qualitative phenomenological approach [44] through a post-intervention focus group. The findings from the statistical analysis and the results of the phenomenological analysis will be integrated, allowing for a more precise understanding of the intervention’s evaluation, its perceived impact, and the acceptability of each modality.

Although this study does not constitute a controlled trial and does not include a no-intervention control group, to ensure methodological rigor and scientific transparency, it has been designed in accordance with the standard items of the SPIRIT 2013 Statement for clinical trial protocols [45] (see Supplementary Materials S1) and takes as a reference the elements of the Trials Registration Data Set (TRDS) [46] considered by the World Health Organization (WHO). In addition, the description of the intervention has been guided by the Template for Intervention Description and Replication (TIDieR) checklist [47] (see Supplementary Materials S2), with the aim of providing a comprehensive, transparent, and replicable account of the intervention components, delivery procedures, materials, and implementation context.

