#### 2.2.5. Participant Retention

Strategies to promote retention in the study will include informational and engagement approaches. An induction session will be conducted to explain the details of the intervention and the schedule of activities, with the aim of reminding the participants of the expected benefits, the importance of their participation, and helping them organize their availability for the program.

Additionally, social incentives linked to Club Tigres will be offered, such as visits to training sessions, match tickets, or interactions with club players.

Participants who accumulate consecutive absences or fail to report viewing the video capsules, whichever the case, will be offered support to continue.

In the case of voluntary withdrawal, the participants will be given the possibility to rejoin the study if feasible; otherwise, they will be considered for future editions of the program.

If a participant leaves the study, their contact information and completed evaluations will be recorded. When possible, they will be asked to complete a survey regarding their experience and reasons for leaving.

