#### 2.3.2. Qualitative Evaluation

A focus group will be conducted with a sample of participants, evenly selected from both modalities, who have provided informed consent. The main topics will be acceptability and perceived contribution in terms of motivation toward physical activity and psychological well-being, with space for suggestions.

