#### 2.5.9. Intervention Adherence

In the face-to-face modality, attendance at sessions will be recorded; to support adherence, reminders and weekly reinforcement messages will be sent to the participants. In the semi face-to-face modality, the participants will report the viewing of the capsules; to encourage adherence, the capsules will be sent with encouraging messages, reinforced with a reminder message, and the participants will submit a screenshot as evidence of capsule viewing.

Only those participants who will have completed both the baseline and post-intervention assessments will be included in the dataset, ensuring that the data reflect actual participation in the program.

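### Acceptability (Objective 5) is determined from a week-13 focus group that mainly reaches participants who stayed, while the planned leavers' survey and adherence records have no part in it

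*Protocol article*

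**What the plan says.** Hypothesis 5 is worded for the programme as a whole and covers both modalities: "The psychoeducational intervention will achieve adequate acceptability, and participants will perceive a positive contribution".

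The evidence for it is described in four places in the protocol article:

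- Section 2.1 says that acceptability and perceived contribution are explored "using a qualitative phenomenological approach [44] through a post-intervention focus group".
- Section 2.3.2 gives the sampling: "A focus group will be conducted with a sample of participants, evenly selected from both modalities, who have provided informed consent".
- Section 2.3.3 gives the timing: "Time 2. Week 13: All instruments and the focus group will be administered". Table 1 agrees.
- Section 2.6.2 gives the basis for the decision: "conclusions from the focus group will be compared with the intervention objectives to determine acceptability and perceived contribution".

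Other information that bears on acceptability is planned elsewhere. Section 2.2.5 says of people who leave that, when possible, "they will be asked to complete a survey regarding their experience and reasons for leaving". Section 2.5.9 says that in the face-to-face modality "attendance at sessions will be recorded", and that semi face-to-face participants report their viewing and send a screenshot. Section 2.7.3 defines acceptability as how participants perceive the structure, content and methodology of PsicoFIT. It names none of these further sources.

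**The concern.** People who find a modality unacceptable have a reason to leave it, and whoever has left by week 13 is unlikely to be in a focus group held alongside the post-intervention questionnaires. A verdict on a modality that rests on this group alone is drawn from a sample partly selected on the quality being judged.

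Hypothesis 5 is not restricted to completers, so a reader will take its conclusion to describe everyone assigned to each modality. Drawing the focus group evenly from the two modalities adds to this. Each modality contributes the same number of voices however many of its 40 participants it has lost, so a retention difference between modalities would not show in the group's make-up. Section 2.1 intends the integrated findings to inform the acceptability of each modality, and that is where the omission would matter.

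**Working it through.** The documents contain no figure on acceptability or expected attrition, so the check is a comparison of the text.

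1. **What decides Hypothesis 5?** Section 2.6.2 names the focus group conclusions. Sections 2.1, 2.3.2 and 2.3.3 describe the same single type of source. Section 2.7.3 adds no other.

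2. **Whom does that source reach?** Section 2.3.2 draws from consenting participants and makes no provision for recruiting people who left. Section 2.3.3 puts the group in week 13 with the Time 2 instruments. Section 2.2.3 counts voluntary leavers, and those who do not complete the instruments, as withdrawn. Section 2.6.1 says that following up non-completers is limited in practice. Taken together, stayers will form most or all of the group. This is an inference, because no sentence excludes leavers.

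3. **Is attrition expected?** Yes. Section 2.6.1 anticipates it. Section 3 lists it as a limitation that may bias results and make the sample less representative, but in general terms and without reference to acceptability. No rate is given.

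4. **Is leaving related to acceptability?** Partly. Section 2.5.11 lists discomfort and lack of time among the reasons a participant may ask to stop. It also lists serious illness and injury, which need not reflect on the intervention.

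5. **Does another step bring leavers back in?** No. Section 2.6.3 integrates the qualitative findings with quantitative results, but sections 2.5.9 and 2.6.1 restrict those results to people with complete data at both times. Neither the leavers' survey nor the adherence records are assigned to any analysis in section 2.6 or any outcome in section 2.7.

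6. **Can the size be worked out?** No. If acceptability were a proportion, the overstatement from hearing only stayers would be

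   share leaving × (proportion favourable among stayers − proportion favourable among leavers).

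   The documents give none of the three terms. The planned output is also a set of themes from constant comparison, not a proportion. The formula shows only the direction: upward whenever some people leave and leavers are less favourable than stayers.

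**The case against.** The strongest reply is that this is a qualitative, non-primary objective. A focus group need not be statistically representative, section 3 already concedes that attrition may bias results, and a journal article commonly leaves the coding of survey text to the full protocol. This stands as far as coding detail goes. It does not remove the point, because the article itself fixes which source determines acceptability, and Hypothesis 5 is stated without limiting it to those who stayed.

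Several stronger readings are tempting, but the documents do not support them:

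- **That leavers are excluded from the focus group.** Section 2.3.2 does not say so, and section 2.2.5 keeps leavers' contact details. Mainly stayers is the likely result, not a stated rule.
- **That the plan can hardly return anything but a favourable verdict.** Section 2.3.2 leaves room for suggestions and section 2.7.3 looks for areas needing adjustment. Stayers can criticise.
- **That the bias can be put in percentage points.** Any such figure would rest wholly on invented rates.
- **That dropout or poor attendance should count against Hypothesis 5 directly.** Participants also receive football fitness and nutrition components, club incentives and reminders. Attendance and dropout therefore reflect adherence to TIGREFIT as a whole, whereas section 2.7.3 defines acceptability as perception of PsicoFIT. A rule that focus group, survey and records must all agree would be unworkable.
- **That one mixed session contaminates the answers.** Section 2.3.2 describes how people are sampled, not how the discussion is composed. Separate sessions are a reasonable preference, not the correction of an error.

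The leavers' survey is itself selective, since it is offered only when possible. It narrows the gap without closing it.

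**Conclusion.** The point holds in limited form. Hypothesis 5 makes a programme-level statement about both modalities, but its stated basis mainly reaches people who stayed, and the planned information about those who left is not used. The conclusion is tilted toward adequate acceptability. This rests on two assumptions: that the week-13 group consists mainly of stayers, which is the natural reading, and that leavers view PsicoFIT less favourably on average, which is plausible but not established. The size of the tilt cannot be derived from the documents. The primary outcomes are not affected. The change is still worth making, because the data are already planned and the conclusion could otherwise be read more widely than its evidence allows.

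**What to change.** In sections 2.6.2 and 2.7.3 of the protocol article:

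1. State that leavers' survey responses on experience and reasons for leaving will be coded with the same constant-comparison categories as the focus group, and will be considered with it when judging Hypothesis 5.
2. Report, by randomised modality, the number of withdrawals with their reasons, together with session attendance or capsule viewing, as supporting context. Note that these also reflect the other TIGREFIT components and that viewing is reported by participants.
3. State that the exit survey will be incomplete. Where leaver data are lacking, limit the Hypothesis 5 conclusion to participants who stayed.

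The cost is a little extra coding of incomplete survey text and a short descriptive table. No new participants or measurements are needed.
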